### Assignment of Interventions: Blinding (Who Will Be Blinded?)

The nature of the intervention is such that participants, treating clinicians, and assessors will not be blinded to group allocation. The project analyst will be blinded to group allocation.

### Data Collection and Management

#### Plans for Assessment and Collection of Outcomes

Treated teeth with intact, sound fillings will be assumed to have arrested decay. The changes will be evaluated through a count of decayed, missing, filled, and arrested decayed tooth surfaces at baseline and 12- and 24-month follow-ups using the International Caries Detection and Assessment System criteria [22]. The assessment will be undertaken by calibrated examiners. Color changes of AgF-treated or AgF- and KI-treated lesions will be evaluated through the classification of the treated lesion into 4 categories according to Pantone color plates. Data will be collected through direct data entry using the REDCap (Research Electronic Data Capture; Vanderbilt University) implementation on iPads (Apple, Inc). The Aboriginal research assistant will assist parents, carers, and children whose primary language is not English in completing the questionnaire.

Parents of the study participants will be invited to take part in focus group interviews at the 12-month follow-up. Consenting parents will be interviewed by the Aboriginal research assistant using a semistructured interview schedule, and the interviews will be digitally recorded. The structured open-ended questions will elicit responses from parents on the care received by their child and follow a yarning approach [12]. The questions will be based on the following:

What were some of the positive aspects of dental care experienced by your child?What were some of the negative aspects of the dental care received by your child?Can you give some examples of what you think could have been done and implemented better during your child’s treatment?Can you name some aspects of the setting, location, and process that you think could have been improved?Can you identify any changes to your oral health knowledge since the research began?

We will also take digital images of the teeth of selected children who provide consent to have the images of their teeth recorded using a smartphone and a standardized protocol [15]. The images will be sent via email, using a secure protocol used within the Western Australia Health Department, to a remote site where an independent, calibrated assessor will assign scores to the images using the same criteria as the field assessment.

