**Methods:**

This study is a cluster-randomized controlled trial with communities randomized and stratified based on caries level and water fluoridation status. The trial will recruit 640 children (aged between 6 months and 7 years) from 30 communities. Informed consent will be obtained. At baseline, each child in the intervention group will be examined by a calibrated examiner and subsequently by an oral health practitioner who will prescribe to an Aboriginal health practitioner the teeth to be treated with AgF. A formulation with 38% AgF will be applied for 1 minute (0.004 mL per tooth). The control group will be provided with standard minimally invasive care. Participants will be followed annually for 2 years to assess caries arrest and prevention by blinded calibrated examiners. Child oral health–related quality of life and dental anxiety will be elicited through validated questionnaires. Tests of proportions will be used to evaluate the proportion of lesions arrested and the proportion of surfaces at risk that decayed over the follow-up. Multiple logistic regression with appropriate control for clustering of teeth and communities will be used to evaluate caries arrest, controlling for potential confounding factors.

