### Objectives

The principal aim of the proposed study is to evaluate the feasibility of using the skills of an appropriately trained Aboriginal health practitioner or worker to undertake the application of AgF to carious primary molars of young Aboriginal children in remote communities and evaluate the effectiveness and acceptability of AgF, using a 2-arm cluster RCT. It will also validate the use of teledentistry to diagnose and prescribe treatment remotely. The outcomes will be compared with those of the alternative care model using the recently tested ART and HT approach, delivered by an oral health professional team, for clinical outcomes, cost-effectiveness, cost utility, child oral health–related quality of life (COHRQoL), and child dental anxiety. The objectives of the project are as follows:

The first objective is to measure the number of teeth and tooth surfaces with arrested carious lesions and restored at baseline and follow-up. The hypothesis is that *the number of arrested carious lesions will be greater in the intervention group at follow-up.*

The second objective is to measure the number of teeth and tooth surfaces with dental decay and new decay and the number of teeth with dental infections among study participants at baseline and follow-up. The hypothesis is that *the number of children with newly active decay in their teeth and tooth surfaces and new dental infections in the intervention group will not be greater than the specified difference (risk difference) deemed to be a noninferior outcome.*

The third objective is to measure the extent of discoloration in teeth treated with AgF, with or without KI. The hypothesis is that *the extent of discoloration will be less in the intervention group treated with AgF and KI.*

The fourth objective is to measure the change in COHRQoL and dental anxiety using validated measures. The hypothesis is that *the extent and number of children with improved COHRQoL and dental anxiety in the intervention group will not be any less than the specified difference (risk difference) deemed to be noninferior.*

The fifth objective is to evaluate the cost-effectiveness and cost utility of the interventions. The hypothesis is that *the intervention will be less costly with a noninferior outcome.*

The sixth objective is to evaluate the acceptability of the interventions between the 2 groups of participants through focus group interviews using the “yarning” approach [12].

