**For Creighton Dental AgF**
Remove food debris and plaque by brushing with a toothbrush (no toothpaste).Isolate teeth to be treated with cotton rolls and gauze and apply petroleum jelly to the gingiva and lips.Dry affected tooth surfaces and at-risk tooth surfaces to be treated with cotton pledgets.Dispense 0.05 mL AgF; bend the microbrush applicator and dip the tip of the applicator into the agent.Apply the agent with the microbrush onto the decayed surface and rub gently, maintaining contact with the tooth for 60 seconds. Apply the agent also to at-risk, nondecayed surfaces for 60 seconds and remove excess from all surfaces with cotton pledgets.Dispense 0.05 mL stannous fluoride. Using a new microbrush, dip the microbrush tip into the stannous fluoride solution and apply it to the decay-treated tooth surfaces.Place Orabase adhesive onto treated decayed surfaces.Advise participant to refrain from eating or drinking for 30 minutes after treatment.

Children allocated to the control group will be provided treatment by the oral health practitioner team (dental therapist and dental clinic assistant). Teeth to be restored using the ART approach will have the decayed tooth surfaces prepared using hand instruments only for caries removal without local anesthesia and teeth restored with a glass ionomer cement. Teeth restored using the HT will have the tooth surface cleaned, but caries will not be removed. The tooth will then be restored with a stainless-steel crown, cemented with a glass ionomer cement. The treating clinician will determine the type of restoration to provide for each control participant.

All the children will be reviewed at 12 and 24 months, and AgF treatments will be reapplied.

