### Outcomes

The primary outcome of interest is the number of treated decayed teeth at baseline that became arrested at each follow-up period and the number of sound surfaces treated at baseline that became carious at follow-ups, measured by the count of decayed, missing, and filled tooth surfaces. Secondary outcomes will be changes in COHRQoL and child dental anxiety (Table 1).

**Table 1 table1:** Standard Protocol Items: Recommendations for Interventional Trials (SPIRIT) participant timeline.

SPIRIT participant timeline		Enrollment	Allocation	After allocation			Closeout
		–T1^a^		Baseline	12 mo	24 mo	

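### The arrest rule for filled teeth depends only on the filling, so as worded it can count a restored tooth as arrested despite an infection or an active surface that the filling does not cover

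*Protocol article*

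**What the plan says.** In the protocol article, Plans for Assessment and Collection of Outcomes opens with a rule for restored teeth: "Treated teeth with intact, sound fillings will be assumed to have arrested decay". The unit is the tooth and the only condition is the state of the filling. Arrest under a filling is assumed, not examined.

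The outcome that this rule feeds is also per tooth. Under Outcomes: "The primary outcome of interest is the number of treated decayed teeth at baseline that became arrested at each follow-up period". The second primary component is per surface: "the number of sound surfaces treated at baseline that became carious at follow-ups, measured by the count of decayed, missing, and filled tooth surfaces".

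Other places use other units:
- The sentence directly after the rule is per surface: "The changes will be evaluated through a count of decayed, missing, filled, and arrested decayed tooth surfaces at baseline and 12- and 24-month follow-ups", scored by International Caries Detection and Assessment System (ICDAS) criteria.
- Objective 1 names both units: "measure the number of teeth and tooth surfaces with arrested carious lesions and restored at baseline and follow-up".
- The abstract is per lesion: "Tests of proportions will be used to evaluate the proportion of lesions arrested".
- Sample Size takes its 61% from ART restorations judged successful.

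Objective 2 records teeth with dental infections, but nothing links that record to the arrest definition. Under Intervention Description, control teeth receive either a glass ionomer filling (ART) or a crown (Hall technique, HT). For the latter, "Teeth restored using the HT will have the tooth surface cleaned, but caries will not be removed".

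**The concern.** The rule is a stated scoring instruction on a primary outcome. Followed as written, it has no exception for two kinds of restored tooth:

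- a tooth whose filling is intact but which has a dental infection at that visit;
- a tooth whose filling is intact but which has another surface, decayed at baseline and not covered by the filling, that is still active.

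Both can be counted as arrested. Restoration is what the control arm receives, whereas AgF-treated lesions normally carry no filling and are judged on the lesion itself. The rule therefore acts mainly on one arm. Any misclassification would raise control-arm arrest and shrink the AgF advantage that objective 1 predicts. It would also count against AgF in a noninferiority comparison of arrest. It could hide a real benefit of AgF, but it would not create a false one.

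**Working it through.** **1. The rule applied to individual teeth at follow-up**

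| Tooth | Tooth-level filling rule | Surface scoring |
|---|---|---|
| Restored; filling intact; a second baseline-decayed surface is uncovered and active | Can be scored arrested | One surface filled, one decayed |
| Two fillings; one intact, one lost with active decay | Arrested only if one intact filling suffices; the plural can mean all fillings | One surface filled, one decayed |
| Filling intact; infection recorded | Arrested | Surfaces alone do not show it; the infection appears under objective 2 |
| Crowned; no infection | Arrested, if a crown counts as a filling (not stated) | No uncovered surface remains |
| AgF; one surface arrested, one active | No rule stated | One arrested, one decayed |

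The uncovered-surface problem is confined to fillings and hardly arises for crowned teeth. For crowned teeth the relevant gap is infection. The table also shows that surface scores alone do not settle a tooth's status, and that the filling rule is the only tooth-level rule given.

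**2. The planned sample size**

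Inputs from Sample Size: control 0.61, AgF 0.81, 80% power, α 0.05 (taken as two-sided), intracluster correlation 0.09, 15 clusters per arm, 25% loss per year.

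- Individually randomised comparison of two proportions: 80 per arm, or 90 with continuity correction.
- With the number of clusters fixed: n = 90 × 15 × (1 − 0.09) / (15 − 90 × 0.09) = 1228.5 / 6.9 = 178.0. That is 12 per cluster, or 180 per arm.
- After loss: 180 / 0.75² = 320 per arm.

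The plan's 180 and 320 reproduce. The point here concerns what is counted as arrested, not this arithmetic.

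**3. What an overstatement would do (assumed sizes)**

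The design effect at 12 per cluster is 1 + 11 × 0.09 = 1.99, so the effective n is 180 / 1.99 = 90.5 per arm. Power is for a two-sided 0.05 test without continuity correction, with AgF held at 81%.

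| Observed control arrest | Difference | Power |
|---|---|---|
| 61% (as planned) | 20 points | about 85% |
| 66% (5 points over) | 15 points | about 63% |
| 71% (10 points over) | 10 points | about 35% |

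**4. Why the protocol does not fix the size**

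Let p be the chance that one lesion is arrested, ρ the within-tooth correlation, and s the share of treated teeth with two lesions. Neither s nor ρ is in the protocol, and using 61% and 81% as per-lesion rates is also an assumption.

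- P(both arrested) = p² + ρp(1 − p), and P(any arrested) = 2p − P(both).
- Control, ρ = 0.5: P(both) = 0.3721 + 0.1190 = 0.491; P(any) = 1.22 − 0.491 = 0.729.
- AgF, ρ = 0.5: P(both) = 0.6561 + 0.0770 = 0.733; P(any) = 1.62 − 0.733 = 0.887.

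With s = 0.4, each arm is 0.6 × p + 0.4 × the two-lesion value:

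| Rule (control / AgF) | Control | AgF | Difference |
|---|---|---|---|
| All lesions / all lesions | 56.2% | 77.9% | 21.7 points |
| Any / any | 65.8% | 84.1% | 18.3 points |
| Any / all | 65.8% | 77.9% | 12.2 points |

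The gap between any and all in the control arm is s × 2p(1 − p)(1 − ρ). For s = 0.2, 0.4 and 0.6 this is about 5, 10 and 14 points at ρ = 0.5, and about 10, 19 and 29 points at ρ = 0. It is zero if the rule means that every filling must be intact and every baseline-decayed surface has been filled. No infection rate is given either. The result depends on the assumptions and on how the rule is read.

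**The case against.** The best defence is that the sentence after the rule prescribes surface-level ICDAS scoring, under which an active second surface is recorded as decayed. Intact, sound fillings, in the plural, can mean that all of a tooth's fillings are intact, which removes the lost-filling case. Infection is a separate outcome under objective 2, and making it override arrest turns arrest into something closer to a composite. Finally, a condensed article may leave to an analysis plan the question of how surfaces combine into a tooth status.

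Much of this stands. A surface-by-surface reading is available, and nowhere does the protocol expressly say that an infected tooth, or one with an active uncovered surface, counts as arrested. A tooth that scores differently on two distinct outcomes is not in itself a contradiction. The rule is also not limited to control teeth, since AgF teeth restored on request would fall under it.

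The defence does not remove the point. The rule is written down, so this is more than missing detail. Surface scoring does not capture infection. For a filled tooth, arrest is inferred and not seen, so a recorded infection on that tooth bears directly on whether the inference is safe.

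A reader might go further and infer that the same partial failure is a success in the control arm and a failure under AgF, cutting the difference from about 22 to 12 points. The protocol does not support that. It gives no every-surface rule for AgF teeth, and the 12-point figure needs the loosest rule in one arm and the strictest in the other. With the loose rule in both arms the difference is about 18 points, close to the planned 20. That model also ignores crowns and single fillings that cover two surfaces.

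**Conclusion.** The point holds as a defect of wording with a possible arm-dependent effect on a primary outcome. The filling rule and the arrest count are per tooth, scoring is per surface, the abstract speaks of lesions, and no override is stated for infection or for an uncovered active surface. Any resulting error would mainly raise control-arm arrest and work against AgF.

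It is not established that control arrest will be overstated. The size cannot be computed from the protocol, and the power figures above only show what assumed overstatements of 5 and 10 points would do. Those figures also take 61% as the control proportion that correct scoring would give, whereas the protocol offers it as a per-restoration success rate. The correction is worth making because it is cheap and because the rule bears on one arm far more than the other.

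**What to change.** Replace the filling sentence in Plans for Assessment and Collection of Outcomes with a rule along these lines: an intact, sound filling or crown counts as arrested only for the baseline-decayed surfaces that it covers; a tooth is scored arrested only if every surface decayed at baseline is arrested or so covered, and no dental infection is recorded for that tooth at that visit; the rule is the same in both arms.

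Then use one unit for the arrest outcome in the abstract, in Outcomes and in Plans for Assessment and Collection of Outcomes, and settle this before any 12-month outcome is derived.

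The cost is one scoring sentence and a few lines of derivation code. Surface scores and infections are already to be collected. The downside is that the control arrest proportion may fall somewhat below the 61% planning figure, and that arrest then carries an infection condition, which should be stated openly when results are reported.

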### Sample Size

We used the *power* command within Stata (version 15; StataCorp) and data on decay incidence, restorative outcomes, and COHRQoL impacts from the recently completed Kimberley study [6] to estimate the noninferiority sample size. Approximately 61% of the ART restorations were classified as successful (lesion arrestment), and 81% were estimated to be arrested with AgF treatment from published studies [19]; community intracluster correlation was 0.09. Using these parameters at 80% power and an α of .05 and with 30 clusters available (n=15, 50% clusters per treatment arm), the estimated sample size required was 180 in each arm. Allowing for a 25% loss to follow-up each year, the estimated sample size is 320 per arm or 22 children per cluster (rounded up). The sample size will also have 84% power to undertake subgroup analyses to detect a 20% difference in caries arrestment between carious lesions treated with AgF and KI or without KI. A sample size of 40 for the focus group interviews is expected to be sufficient to allow for the elicitation of parent perceptions about the care provided based on our earlier work [20,21].

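### Arrest is inferred from an intact restoration in control teeth but observed on the open lesion in AgF teeth, so the arrest result needs a companion outcome scored the same way in both arms

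*Protocol article*

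**What the plan says.** Under Outcomes, part of the primary outcome is "the number of treated decayed teeth at baseline that became arrested at each follow-up period". The first hypothesis, under Objectives, is that "the number of arrested carious lesions will be greater in the intervention group at follow-up".

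Plans for Assessment and Collection of Outcomes gives the scoring convention, "Treated teeth with intact, sound fillings will be assumed to have arrested decay", and says change will be measured by "a count of decayed, missing, filled, and arrested decayed tooth surfaces at baseline and 12- and 24-month follow-ups" using ICDAS criteria.

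Intervention Description sets out what is done to the tooth. Control teeth get either a glass ionomer filling after hand-instrument caries removal (ART) or a cemented stainless-steel crown (HT). Of the latter it says: "Teeth restored using the HT will have the tooth surface cleaned, but caries will not be removed". The textbox steps for both AgF products end with an adhesive paste over the treated lesion. Neither includes a filling.

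Sample Size takes its control rate from restorations, "Approximately 61% of the ART restorations were classified as successful (lesion arrestment", and its AgF rate from lesions, "81% were estimated to be arrested with AgF treatment from published studies". It adds that the "community intracluster correlation was 0.09".

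**The concern.** The word arrest covers two different observations. In an AgF tooth the lesion is open and the examiner judges it arrested or active. In a control tooth with a sound restoration the lesion cannot be seen, and arrest is credited because the restoration is intact. With HT, decayed tissue is known to be present beneath the crown, so the credit is wholly an inference. (The convention speaks of fillings. I read it as extending to crowns, since a crowned lesion cannot be scored any other way.)

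The first hypothesis is a claim that AgF arrests more decay. If the arms are measured on different scales, it could be accepted or rejected because restorations survive at a different rate from that at which lesions harden, and not because of what AgF does to decay. Analysing by intention to treat and per protocol does not help, because both sets use the same scoring.

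**Working it through.** **1. What is scored in each arm, as allocated**

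- AgF lesion: open, scored arrested or active under the ICDAS-based count. Observed.
- Control tooth, restoration intact: scored arrested by convention. Inferred.
- Control tooth, restoration lost or defective: no separate rule is stated. The general surface count, which has an arrested category and is not limited to one arm, would naturally apply.

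The convention refers to treated teeth in general. An AgF-arm tooth restored later, through other care by the oral health team (Intervention Description) or at the family's request (Criteria for Discontinuing or Modifying Allocated Interventions), falls under it too. As allocated treatment, however, it acts almost only on the control arm.

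**2. The planned sample size rests on the two quantities**

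Inputs from Sample Size: 61% v 81%, α 0.05 (taken as two-sided), 80% power, ICC 0.09, 15 clusters per arm, 25% loss per year.

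- Individually randomised, two-sided, continuity-corrected comparison of proportions: n = 90 per arm.
- Cluster size: m = n(1 − ICC)/(K − n × ICC) = 90 × 0.91/(15 − 8.1) = 81.9/6.9 = 11.87, rounded up to 12.
- 12 × 15 = 180 per arm, as stated.
- 180/0.75² = 180/0.5625 = 320 per arm, as stated.

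The arithmetic is sound. It confirms that the planned contrast is ART restoration success against AgF lesion arrest.

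**3. Effect of the stated convention alone**

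Let q be the share of intact control restorations that cover active decay. The article gives no figure, so q is assumed. True control arrest = 0.61 × (1 − q), and the true gap is 0.81 minus that.

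| q | true control arrest | true gap |
|---|---|---|
| 5% | 0.61 × 0.95 = 58.0% | 23.1 points |
| 10% | 0.61 × 0.90 = 54.9% | 26.1 points |
| 20% | 0.61 × 0.80 = 48.8% | 32.2 points |

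So the convention flatters the control arm and works against the first hypothesis.

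**4. The opposite direction, only under a rule that is not stated**

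If failed restorations were scored as not arrested, and a share s of them in fact lay over arrested tissue, true control arrest would be 0.61 + 0.39 × s. For s = 25% this is 70.8%; for s = 50%, 80.5%. The 20-point gap closes at s = 0.20/0.39 = 51%. The value of s is also assumed.

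In steps 3 and 4, 61% is a planning figure for ART restorations only. The control arm will also contain crowns, in a mix chosen by the treating clinician, so these numbers illustrate sensitivity and do not estimate bias in the trial's result.

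**The case against.** The strongest reply is that the convention is openly stated and some inference is unavoidable when a covered lesion is compared with an open one. Filled and arrested surfaces are already separate categories in the count, so arrest can be re-analysed with and without fillings. The second objective already measures decay, new decay and dental infection in both arms. How crowns and defective fillings are scored belongs in an examiner manual or analysis plan, and a journal article need not carry it. The figures of 180 and 320 reproduce, so no number is wrong.

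Most of this stands. No arithmetic error is alleged, and the absence of a scoring rule for failed fillings is not itself a fault of a condensed article. What remains is a stated convention that merges the two categories for the headline comparison. Being able to separate them later is not the same as prespecifying it. The second objective is also not a result for the treated decayed tooth itself.

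A reader might go further and infer that the whole planned 20-point advantage for AgF could be a measurement artefact. The documents do not support that. It requires failed fillings to count as not arrested, which Sample Size implies by equating success with arrest but the outcome section never says. It also needs about half of failed restorations to lie over arrested tissue, a share given nowhere. The convention that is stated pushes the other way. Nor can it be said that such errors are impossible in the AgF arm, since AgF-arm teeth that are restored come under the same convention.

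**Conclusion.** The point holds as a problem of comparability. The arrest part of the primary outcome sets inferred arrest under restorations against observed arrest of open lesions, and the sample size is built on the same pairing.

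The stated convention alone would, if anything, overstate control arrest: 61% would become 58% to 49% if 5 to 20% of intact restorations hid active decay. Those shares are assumed, and 61% excludes crowns. A bias towards AgF depends on a scoring rule that is not stated. The net direction and size are therefore undetermined from the documents, and both analysis sets carry whatever bias there is. The finding limits what a result of more arrest, or of no difference, could be taken to mean. It does not show that the trial's conclusion would be wrong. The change is a cheap improvement worth making before recruitment.

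**What to change.** 1. Beside the arrest analysis, prespecify a tooth-level outcome assessed by the same examination in both arms: treated tooth free of visible active caries, infection, extraction for caries and retreatment, at 12 and 24 months. Because AgF is scheduled for reapplication at both visits, define retreatment as treatment beyond that schedule. Tabulate the components, since a cover can still hide decay while infection, extraction and retreatment are equally detectable in both arms. Interpret the first hypothesis in light of both results.
2. Report intact restoration and observed arrested lesion as separate categories, with a sensitivity analysis of arrest under both scorings (intact restorations counted as arrested, and not so counted).
3. Confirm that a lesion exposed by a lost or defective restoration is scored arrested or active by the same criteria as an AgF lesion.
4. In Sample Size, describe the 61% as restoration success.

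The cost is one extra analysis of data the planned examinations and treatment enquiries already produce, plus a line in examiner training. The Results section says calibration is in progress and recruitment is planned from March 2026. The downside is that a superiority claim on arrest becomes slightly harder to make.

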#### Intervention Description

Children allocated to the test group will be provided with AgF, either Riva Star Aqua (38% AgF and KI) or Creighton Dental AgF (40% AgF and stannous fluoride). Only the primary molars will be included. The AgF will be applied by an Aboriginal health practitioner or worker who has been trained in the application of fluoride agents. The agents will be applied once only, after baseline assessment, and repeated at the 12- and 24-month follow-ups. All other treatments required beyond AgF application will be managed by the oral health practitioner team. Interventions for Riva Star Aqua and the Creighton AgF are outlined in Textbox 1.

Interventions for Riva Star Aqua and the Creighton silver fluoride (AgF).

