#### Criteria for Discontinuing or Modifying Allocated Interventions

Participants allocated to the test arm (AgF treatment) who request restorative care as per the control arm (ART and HT treatment) will be provided with the requested care. Similarly, control participants who request the test intervention will be provided with the test intervention. The reasons for the request will be noted. All participants will be analyzed on an intention-to-treat and per-protocol basis.

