#### Relevant Concomitant Care Permitted or Prohibited During the Trial

All participants will be able to access and receive regular dental care from their usual dental care provider. Information regarding treatment received during the follow-up interval will be sought from participants at each follow-up.

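### Scoring any treated tooth with an intact filling as arrested lets a treatment failure that was later filled count as a success, in either arm

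*Protocol article*

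**What the plan says.** The Outcomes section makes the primary outcome "the number of treated decayed teeth at baseline that became arrested at each follow-up period", together with new caries on sound treated surfaces. Plans for Assessment and Collection of Outcomes then adds the scoring rule: "Treated teeth with intact, sound fillings will be assumed to have arrested decay". The rule has no limit by arm, by date, or to the restoration placed as allocated treatment.

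Three sections allow an AgF-treated tooth to be filled later:
- Criteria for Discontinuing or Modifying Allocated Interventions covers care on request: "Participants allocated to the test arm (AgF treatment) who request restorative care as per the control arm (ART and HT treatment) will be provided". Reasons for the request are noted, and switching is also allowed from control to AgF.
- Intervention Description: "All other treatments required beyond AgF application will be managed by the oral health practitioner team".
- Relevant Concomitant Care: "All participants will be able to access and receive regular dental care from their usual dental care provider".

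The last section also says "Information regarding treatment received during the follow-up interval will be sought from participants at each follow-up", but no section says that this information alters the arrest score. On analysis sets the article says "All participants will be analyzed on an intention-to-treat and per-protocol basis".

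**The concern.** An AgF-treated lesion may stay active, be filled, and carry a sound filling at the next examination. Followed as written, the rule scores that tooth as arrested and credits it to AgF under intention-to-treat. A control restoration that failed and was replaced is scored the same way. The outcome then mixes the effect of the allocated treatment with the effect of rescuing it.

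Arrest is the outcome on which the sample size rests. The article calls that calculation a noninferiority one, while its first objective expects more arrest with AgF. Under either reading the rule matters: shrinkage of a true deficit makes noninferiority easier to claim, and shrinkage of a true advantage costs power.

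**Working it through.** **Inputs from the article (Sample Size).** Control arrest 61%, AgF arrest 81%, intracluster correlation 0.09, 15 clusters per arm, 80% power, α 0.05, 25% loss per year for two years.

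**The plan's own figure.** A two-sided, continuity-corrected comparison of 61% v 81% needs n = 90 per arm without clustering. Children per cluster: m = n(1 − ρ)/(K − nρ) = 90 × 0.91/(15 − 8.1) = 11.87, rounded to 12, so 12 × 15 = 180 per arm. Loss: 180/(0.75 × 0.75) = 320. Both stated figures reproduce. The scoring rule does not make them wrong; it changes what the 61% and 81% would mean when observed.

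**Effect of the rule.** Let a and c be the true AgF and control arrest rates, and fA and fC the shares of failures that are later filled and intact at the examination.
- Observed AgF = a + (1 − a)fA; observed control = c + (1 − c)fC.
- Net bias in the difference = fA(1 − a) − fC(1 − c).
- With fA = fC = f, observed difference = (a − c)(1 − f).

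The documents do not give f. The values below are assumptions.

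| True AgF v control | fA, fC | Observed | Difference: true → observed |
|---|---|---|---|
| 81% v 61% | 20%, 20% | 84.8% v 68.8% | +20 → +16.0 |
| 81% v 61% | 30%, 30% | 86.7% v 72.7% | +20 → +14.0 |
| 61% v 61% | 20%, 20% | 68.8% v 68.8% | 0 → 0 |
| 51% v 61% | 25%, 25% | 63.25% v 70.75% | −10 → −7.5 |
| 61% v 61% | 20%, 0 | 68.8% v 61% | 0 → +7.8 |
| 61% v 61% | 30%, 0 | 72.7% v 61% | 0 → +11.7 |

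**Cost in power if arrest is tested for superiority.** The design effect is 1 + 11 × 0.09 = 1.99, so 180 per arm is worth 180/1.99 = 90.5. With the same continuity correction, power = Φ{[(d − 1/90.5)√90.5 − 1.96√(2p̄(1 − p̄))]/√(a(1 − a) + c(1 − c))}, where d is the observed difference, a and c here are the observed rates and p̄ is their mean. This gives 81% at 81% v 61%, 66% at 84.8% v 68.8%, and 58% at 86.7% v 72.7%, with the intracluster correlation held at 0.09.

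**The case against.** The strongest case against has five parts.

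- **A narrower meaning.** The sentence may only be meant to place control ART restorations on the arrest scale, since the Sample Size section equates a successful ART restoration with arrest. That is plausible, but the wording does not say so. If it is the intent, a few words settle it.
- **Detail left to a fuller document.** Derivation rules often sit in the full protocol or analysis plan. Here, however, the article states a rule, and the rule as stated is too broad.
- **Low exposure.** The article says most decay goes untreated and access to dentists is poor. The stated action for AgF teeth at review is reapplication. If examination precedes treatment at review, as at baseline, a filling placed at 12 months affects only the 24-month score. This suggests that f may be small at 12 months. It does not close the routes, two of which run through the trial itself.
- **Net direction.** A reader might infer that the rule simply inflates AgF by 8 to 12 points. The documents do not support that: the rule applies to both arms, and that figure needs fA to exceed fC by 20 to 30 percentage points. At equal shares and the planning rates, the rule reduces the AgF advantage. This objection stands.
- **Switching is not failure.** The article names staining as the major disadvantage of AgF, so a restoration on request may follow an arrested lesion. Scoring every such tooth as failed would bias against AgF. This also stands and shapes the remedy.

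**Conclusion.** The rule as written is faulty and should be changed. It can only raise the observed arrest rate in each arm, by f times that arm's failure rate. The net effect on the difference is not fixed in direction. With equal shares it moves the difference towards zero: 20 points become 16 or 14 at f of 20% or 30%, and a 10-point AgF deficit becomes 7.5 at f of 25%. The latter favours AgF in a noninferiority comparison. Only if failures are filled more often in the AgF arm does the bias favour AgF directly. The 8 to 12 points are the case with no later filling of control failures. All the shares are assumed.

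A reader might also infer that intention-to-treat and per-protocol err the same way, so that agreement between them means nothing. That would follow if the per-protocol set drops children who switched, but the article does not define the set. Whether it corrects the problem cannot be told.

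**What to change.** Amend the outcome definition as follows. None of this alters the care given.

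1. Apply the rule that an intact filling means arrest only to the restoration placed as the allocated baseline treatment.
2. In both arms, score as not arrested any tooth decayed and treated at baseline that later had a new or replacement restoration, pulp treatment or extraction because of active caries, restoration failure or infection. Use the interval-treatment data and the recorded reasons for switching.
3. For teeth restored on request for other reasons, such as appearance, carry the last arrest status recorded before the restoration. Use not arrested as a sensitivity analysis. State what applies when no status after treatment exists yet.
4. Report the current rule as a further sensitivity analysis.

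The cost is outcome wording, one derived variable, and coding of the reason for each interval treatment, which the article does not yet ask for outside switching. Stated arrest rates will fall somewhat in both arms.
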